### Trial design {8}

This is a parallel-arm, open, stratified randomized clinical trial. Forty-six overweight or obese women diagnosed with PCOS will be randomly stratified to receive either PLCD or KD for 8 weeks.

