### Outcomes {12}

#### Primary outcomes

The primary outcome of this investigation is to determine the effectiveness of the PLCD compared to the KD in improving PCOS disease symptoms by measuring weight loss before and after the intervention.

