### Sample size {14}

According to the formula, the standard deviation of weight in the dietary group of PLCD and KD would be equal to μ_1_ = 3.14 (σ_1_ = 2.42) and μ_2_ = 1.66 (σ_2_ = 0.8) respectively. In the following sample with *α* = 0.05, the sample size required to have 80% power to detect a difference of 2 units of change in weights would be 18 people in each group. Considering the possibility of 25% missing people in the follow-up, the sample size increases to 23 people in each group.$$n=\frac{{\left({z}_{1-\frac{a}{2}}+{z}_{1-\beta }\right)}^{2}+\left({\sigma }_{2}^{1}+{\sigma }_{2}^{2}\right)}{{\left({\mu }_{1}-{\mu }_{2}\right)}^{2}}$$

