## Statistical methods

### Statistical methods for primary and secondary outcomes {20a}

Data analysis will be done using SPSS Statistics (version 19, NY, USA). A two-tailed statistical significance will be accepted at *P* < 0.05. Each outcome variable assessed will be analyzed according to diet (PLCD or KD) and time (before and after each diet) using a repeated-measures two-way analysis of variance (ANOVA). Where appropriate, a Student–Newman–Keuls post hoc test will be used to assess the origin of any significant differences detected by the ANOVA models. Variables will be adjusted for potential confounders which will be determined using multiple linear regressions.

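### The Student–Newman–Keuls step does not fit a two-diet, two-time ANOVA, and its open trigger lets the diet main effect be read as the diet comparison

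*Protocol article*

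**What the plan says.** Section {20a} of the protocol article, on statistical methods for primary and secondary outcomes, states that each outcome "will be analyzed according to diet (PLCD or KD) and time (before and after each diet) using a repeated-measures two-way analysis of variance (ANOVA"). Each factor therefore has two levels. The next sentence adds, where fitting, that "a Student–Newman–Keuls post hoc test will be used to assess the origin of any significant differences detected by the ANOVA models". The section names no term of the model as the test of PLCD against KD.

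The quantity of interest appears elsewhere. The primary outcome compares the two diets "by measuring weight loss before and after the intervention", and Sample size {14} powers the trial on a difference in weight change. Trial design {8} reads: "This is a parallel-arm, open, stratified randomized clinical trial". Each woman therefore contributes two weights under one diet.

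The section Data management and analysis gives a second method for comparing means within and between groups: Student's t-test, or Wilcoxon and Mann–Whitney tests when data are not normal. It does not say whether final values or changes are compared.

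**The concern.** A Student–Newman–Keuls test locates differences among three or more means. A 2 × 2 layout has no such set within either factor. The only set of more than two means is the four diet-by-time cells, and comparing those in pairs does not answer the trial's question. The question is whether change differs between diets. That is the one-degree-of-freedom diet × time contrast, which needs no post hoc step.

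The trigger is also wide. Any significant ANOVA term may be followed up, so a significant diet main effect could be reported as one diet being better. That term compares the average of each woman's before and after weights, which is almost entirely baseline weight. At stake is whether the conclusion on the better diet, for weight and every other outcome, rests on a quantity that measures the diet effect.

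**Working it through.** **Inputs from the document.** Sample size {14}: weight changes of 3.14 (SD 2.42) and 1.66 (SD 0.8), two-sided alpha 0.05, 80% power, a target of 2 units, 18 per arm, 23 after dropout. **Assumed, because not given:** between-woman weight SD of 10–15 kg, normal data, and change independent of baseline.

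**The plan's own figure.** Average change variance is (2.42² + 0.8²)/2 = (5.8564 + 0.64)/2 = 3.248, so SD 1.802. The planning difference is 3.14 − 1.66 = 1.48. The standard formula, (1.960 + 0.842)² × 6.4964 / difference², gives 7.849 × 6.4964 / 2.190 = 23.3, so 24 per arm. For a difference of 2 it gives 12.7, so 13. The stated 18 is not reproduced. That is a separate matter, and 18 is used below only as the planned number of completers per arm.

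**1. Post hoc test on a two-level factor.** For two means the critical value is q/√2. At 34 df this is 2.032, equal to the t value at 34 df; at 44 df both are 2.015. The post hoc test therefore repeats the F test.

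**2. Post hoc test on the four cells.** The six pairs are:
- baseline against baseline;
- week 8 against week 8;
- before against after in each arm (two pairs);
- one arm's before against the other arm's after (two pairs).

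The difference in change is a contrast of all four cells and is not among them. The procedure also treats the means as independent, while before and after come from the same women.

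**3. Diet × time against the diet main effect, 18 per arm.**
- Diet × time: effect 1.48, standard error 1.802 × √(2/18) = 0.601, ratio 2.46.
- Diet main effect: the effect is halved to 0.74. The SD of a woman's average is √(SD² + 3.248/4). At SD 10 this is 10.04, standard error 3.35, ratio 0.22. At SD 15 it is 15.03, standard error 5.01, ratio 0.15.

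Simulation (20,000 trials per setting) gives power of about 67% for diet × time and 5–6% for the main effect. At a true difference of 2, diet × time has about 90% power and the main effect still only about 6% (SD 12 or 15 kg).

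**4. Either term counted as a diet effect, no true difference.** If the two tests were independent, the false-positive rate would be 1 − 0.95² = 9.75%. Simulation gives about 10%.

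**5. Four-cell test with no diet effect** (common loss 2.4 kg, SD 1.8, within-woman residual as error term). The time effect is then almost always significant: with 36 women, t = 2.4/(1.8/√36) = 8. Simulated rates of falsely separating the arms at week 8:

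| Term that must be significant first | False separation |
|---|---|
| Any term, including time | about 80–86% |
| Diet or diet × time | about 9% |
| Diet × time only | about 4% |

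With the pooled cell variance as error term instead, the four-cell test finds the week-8 difference in only 3–4% of trials when the true difference is 1.48.

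**The case against.** The strongest defence is that the sentence is harmless boilerplate. It applies only where fitting and only after a significant ANOVA result. On a main effect it repeats the F test, and after a significant interaction the question is already answered. The target can be recovered from the primary outcome and sample size sections, so a careful analyst would choose diet × time. Naming the model term is also something an article may leave to an analysis plan. The main effect keeps its own 5% error rate over randomisations.

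Much of this stands. The missing name of a term would not be a finding by itself. What remains is a stated rule that does not fit the design, with a trigger that excludes no term, beside a second stated method for the same comparisons.

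A reader might infer that the plan would falsely declare a diet difference in 80–86% of null trials. The document does not support that. The figure needs a significant time effect to license diet comparisons, a four-cell test, and a within-woman error term applied to a between-women comparison. The article prescribes neither the four-cell test nor that error term. A reader might also infer from the description of the time factor that each woman takes both diets. The trial design section rules this out, and the phrase is only awkward.

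**Conclusion.** The point holds at moderate size. The post hoc step is either redundant or aimed at comparisons that are not the difference in change, and the open trigger leaves the diet main effect available as a diet claim. At the planning values that term has about 5–6% power against about 67% for diet × time, and accepting either term roughly doubles the false-positive rate to about 10%. These figures assume 18 completers per arm and a between-woman weight SD of 10–15 kg. An SD of 8 kg gives about 6% for the main effect and 67% for diet × time, so the conclusion does not turn on that choice. The 67% reflects the planning difference of 1.48; it is not caused by the post hoc test. The four-cell false-separation rate depends on the trigger, about 4%, 9% or 80–86%, and should be cited only with that condition.

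**What to change.** In section {20a}:
- Delete the Student–Newman–Keuls sentence.
- Name one test of the diet comparison for each outcome. Either the diet × time contrast, reported as the difference in mean change with its 95% confidence interval, or the week-8 value compared between diets with adjustment for baseline (ANCOVA) would serve.
- State that the diet main effect and the cell comparisons are not used for conclusions.
- Reconcile this with the t-test and Wilcoxon/Mann–Whitney plan under Data management and analysis, so that a single method governs the diet comparison.

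The cost is the wording of one paragraph. No extra data or participants are needed for this change.

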### Interim analyses {21b}

No interim analyses will be performed.

### Methods for additional analyses (e.g., subgroup analyses) {20b}

We intend to perform subgroup analysis, such as fat body mass vs. lean body mass, LDL vs. HDL, testosterone vs. luteinizing hormone (LH). We will try to match for most variables across groups. Adjustments will be made for confounding factors like waist circumference, macronutrients consumption, and physical activity.

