## Intervention description {11a}

### Dietary intervention

A PLCD is a plant-based diet with a macronutrient distribution of 40% carbohydrate, 20% protein, and 40% fat. The Portfolio diet consists of four food components added to the diet (based on a 2000 kcal diet): 50 g plant protein from soy products or dietary pulses such as beans, peas, chickpeas, and lentils; 20 g viscous soluble fiber from oats, barley, psyllium, eggplant, okra, and certain fruit; 45 g nuts (tree nuts or peanuts); and 2 g phytosterols. Later on, a fifth component was joined to the diet, as plant-based monounsaturated fats (MUFAs) in the form of olive, canola, or high oleic sunflower oils (45 g/day) that indicated more improvements of blood lipids, such as high-density lipoprotein (HDL) and cholesterol [26]. So, each diet will be determined according to the prescribed daily calorie and macronutrient intake. On the other hand, the KD contains 10% carbohydrates, 20% protein, and 70% fat. Carbohydrates intake will be < 30 g per day which will be provided by a variety of vegetables as they ate rich in fiber and have low amounts of carbohydrates. Protein intake will be provided through fish, poultry, meat, and egg consumption. Furthermore, lipid components will be consumed in the form of olive oil, sesame, and oilseeds. Unsweetened drinks like herbal teas, tea, and infused coffee will be allowed as they would not induce ketosis. Both groups will take a multivitamin-mineral supplement (Dana Corp. Multi Daily) every day. Each patient will have at least ninety minutes of dietary counseling with a dietitian to educate their diet, be encouraged to have aerobic physical activity, for instance, walking or jogging at least 60 min per day, and be remined to stop continuing the diet if they realized that they are pregnant. To induce patients’ motivation of following their diet, the dietitian will assure them to prescribe a stabilized diet at the end of the study. Furthermore, the dietitian will be readily available to guide and advise individuals via phone, email, and other media.

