#### Secondary outcomes

The secondary outcomes are including body mass index (BMI), fat body mass (FBM), lean body mass (LBM), body fat percentage, waist circumference, insulin level as well as sex hormones (testosterone, LH, FSH, DHEA), lipid profile (cholesterol, triglycerides, low-density lipoprotein (LDL), high-density lipoprotein (HDL)), glucose levels, HOMA index – IR, physical activity, health-related quality of life (SF-36), and Ferriman-Gallwey score, before and after the intervention.

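### The covariates named for adjustment are not limited to baseline, and their on-study values are the randomised contrast or outcomes, so adjusting for them can strongly attenuate or blur the diet effect

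*Protocol article*

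**What the plan says.** Three statements on adjustment and subgroups matter.

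- Additional analyses {20b}: "Adjustments will be made for confounding factors like waist circumference, macronutrients consumption, and physical activity". No time of measurement is given.
- Statistical methods for primary and secondary outcomes {20a}, after the diet-by-time ANOVA: "Variables will be adjusted for potential confounders which will be determined using multiple linear regressions". No covariate is named there.
- Additional analyses {20b} again: "We intend to perform subgroup analysis, such as fat body mass vs. lean body mass, LDL vs. HDL, testosterone vs. luteinizing hormone (LH".

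Elsewhere the same document gives these variables other roles.

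- Dietary intervention {11a} defines the portfolio arm by a "macronutrient distribution of 40% carbohydrate, 20% protein, and 40% fat" and states that "the KD contains 10% carbohydrates, 20% protein, and 70% fat".
- Dietary monitoring {11c} collects 3-day food records every 2 weeks so that the dietitian can see how well the diet is followed.
- Secondary outcomes {12} include "body fat percentage, waist circumference, insulin level as well as sex hormones" and "physical activity, health-related quality of life (SF-36), and Ferriman-Gallwey score, before and after the intervention".
- Baseline measures {18a} include waist circumference, the physical activity questionnaire and 3-day food records, so a pre-randomisation value of each variable exists.

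**The concern.** A confounder of a randomised comparison can only be something present before allocation that happens to differ between the arms. The values of the three named variables during or after the diet do not qualify.

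- **Macronutrient intake on the diet** is the treatment as received. Holding it fixed asks whether the arms differ among women eating the same macronutrients, which is close to asking nothing. It also sits badly with the intention-to-treat analysis in {20c}.
- **Waist circumference after baseline** moves with weight. Holding it fixed takes out part of the outcome itself.
- **Physical activity after baseline** is a listed outcome that diet might affect.

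Section {20a} adds a second difficulty. If regression on the trial's own data decides which confounders enter, the result with 46 women can depend on which model is selected.

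At stake is the unbiased randomised comparison. An analyst could follow the text as printed and largely cancel the contrast under test.

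**Working it through.** The plan gives no figure for the effect of adjustment, so there is none to reproduce. The checks below show how much the time of measurement matters.

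**Inputs from the protocol.** Carbohydrate share is 40% and 10% by arm {11a}. There are 23 women per arm {15}. The sample-size section {14} gives means 3.14 and 1.66 with SDs 2.42 and 0.8, so the gap between means is 3.14 − 1.66 = 1.48. The same section powers for a difference of 2 units.

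**Inputs assumed, because the protocol gives none.** The within-arm SD of on-diet carbohydrate share is 5 to 10 percentage points, with both arms achieving their target on average. The correlation r between waist change and weight change is 0.5 to 0.85.

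**1. On-diet carbohydrate share as covariate.** With equal arms the arm means lie 15 points either side of the overall mean, so the variance inflation factor for the diet effect is 1 + 15²/SD².

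- SD 5: 1 + 225/25 = 10.0, standard error × 3.2
- SD 8: 1 + 225/64 = 4.5, standard error × 2.1
- SD 10: 1 + 225/100 = 3.25, standard error × 1.8

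**2. Waist change as covariate.** Take waist change as proportional to weight change plus independent noise.

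- Average within-arm variance of weight change: s² = (2.42² + 0.8²)/2 = 3.248.
- Variance over both arms together: V = 3.248 + (1.48/2)² = 3.796.
- For an overall correlation r, the noise variance in weight units is e = V(1/r² − 1).
- The adjusted diet effect is 1.48 × e/(s² + e).

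| r | e | Adjusted effect (unadjusted 1.48) |
|---|---|---|
| 0.5 | 11.39 | 1.15 |
| 0.7 | 3.95 | 0.81 |
| 0.85 | 1.46 | 0.46 |

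If r is instead the within-arm correlation, the adjusted effect is 1.48 × (1 − r²) = 1.11, 0.75 and 0.41. If the true difference is the 2 units of {14}, V = 3.248 + 1 = 4.248 and the overall-correlation results are about 1.59, 1.15 and 0.67.

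**3. Baseline against on-study values.** A simulation of 4,000 trials used 23 women per arm and a true difference of 2 kg in weight change. It assumed that the effect acts wholly through carbohydrate share, that the within-arm SD of that share is 5 points, and that waist changes by 0.9 cm per kg.

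| Adjusted for | Mean difference (kg) | Power |
|---|---|---|
| nothing | −2.00 | 95% |
| baseline waist | −2.00 | 95% |
| baseline carbohydrate | −2.00 | 95% |
| change in waist | −0.92 | 63% |
| on-diet carbohydrate | 0.03 | 5% |
| on-study waist, carbohydrate and activity | 0.02 | 5% |

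With on-diet carbohydrate in the model, the standard error rises from 0.54 to 1.70. This agrees with the factor of about 3.2 in step 1.

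**4. Subgroups.** Fat and lean mass, LDL and HDL, and testosterone and LH are all secondary outcomes {12}. Each pair is two measurements on the same woman. Neither member divides the women into groups, so no subgroup effect can be estimated from it.

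**The case against.** The strongest reply is that {20b} never says on-study values will be used. All three variables are measured at baseline, and the sentence follows one about matching the groups on most variables, which suggests baseline imbalance. On that reading nothing is lost, as the baseline rows of the simulation show. This stands. A reader might infer that the plan's adjustment does remove the diet effect, but the document supports only that it can.

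Four further limits also stand.

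- Being a secondary outcome does not disqualify a variable as a covariate. Its baseline value is legitimate, and only the later value is a problem.
- The three variables are named only under additional analyses. Section {20a} extends confounder adjustment to the primary and secondary outcomes but names no covariate, so it is an inference that these three enter the primary model.
- Post-baseline waist might be called a step on the path from diet to weight. Waist change accompanies weight loss rather than causing it, and the bias arises because it is a proxy for the outcome. For physical activity no path is shown, since both arms receive the same encouragement.
- The figure 1.48 is the gap between the stated means, not the difference the trial is powered for. The SDs of intake and the correlations have no source in the document.

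The reply does not remove the ambiguity. No section confines covariates to baseline. Food records are also taken during the diet, and waist and activity are measured again afterwards. Section {20a} leaves the choice of confounders to regression.

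**Conclusion.** The point holds in conditional form. The plan labels as confounders the variable that defines its arms and two of its outcomes, does not restrict them to baseline, and lets regression on the trial data choose confounders for the primary and secondary outcomes.

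If on-study values are used, the harm can be large. Variance inflation is 3.3 to 10 for on-diet carbohydrate share. A 1.48 difference shrinks to about 1.15 to 0.46 when waist change is a covariate. The simulated effect is lost entirely when it acts wholly through carbohydrate share and on-diet intake is a covariate. The sizes rest on the assumed intake SDs, correlations and mediation. That such adjustment no longer estimates the effect of assignment to diet does not depend on them. If only baseline values are used, none of this harm arises.

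The outcome-pair subgroups are a separate and lesser fault. They cannot be run as subgroup analyses, but they do not threaten the diet estimate.

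**What to change.** Replace the adjustment sentences in {20a} and {20b} with one rule: the diet comparison is adjusted only for prespecified baseline covariates, namely the baseline value of the outcome and any randomisation strata. Covariates are not selected from the trial data, and no variable measured after randomisation enters the primary or secondary comparisons.

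Report on-study intake and physical activity descriptively by arm, or in an analysis labelled as exploratory mediation. Such an analysis need not be forbidden, only kept apart from the main comparisons.

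Delete the outcome-pair subgroups from {20b}. No replacement subgroup is required.

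The cost is rewording two paragraphs. No new data, visits or participants are needed.

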### Methods in analysis to handle protocol non-adherence and any statistical methods to handle missing data {20c}

An “intention to treat” analysis will be conducted to handle protocol non-adherence. In the case of more than 10% missing for the primary outcome, we plan to impute missing values using the multiple imputation method.

### Plans to give access to the full protocol, participant level-data and statistical code {31c}

This trial does not have any plan for giving access to the full protocol, participant-level data, and statistical code.

## Oversight and monitoring

### Composition of the coordinating center and trial steering committee {5d}

All research team members will collaborate in preparing all the study steps.

### Composition of the data monitoring committee, its role and reporting structure {21a}

All research team members will collaborate in preparing all the study steps.

### Adverse event reporting and harms {22}

As previously mentioned, these two diets do not have serious adverse or harmful effects on short time. It seems that the ketogenic diet demonstrates some adverse events (AEs) such as dehydration, hypoglycemia, lethargy, and gestational side effects (diarrhea, nausea, and vomiting) for a short time and serious adverse effects (SAEs) like hypercalcemia, lipid profile change, urolithiasis, gallstone, and hair loss for long-term intervention. Since our trial will be conducted for a short time (8 weeks), it is predicted to have no SAEs. However, each participant will be informed of the side effects of their diet by a dietitian and will be reminded to stop the diet if they experience any AEs or discover they are pregnant. Moreover, SAEs will be reported to the DMEC, indicating expectedness, seriousness, severity, and causality.

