### Criteria for discontinuing or modifying allocated interventions {11b}

There have not been observed serious complications for PLCD [27]. Furthermore, there have been reported some short-term and long-term complications for the ketogenic diet. Short-term complications are dehydration, hypoglycemia, lethargy, and gestational side effects (diarrhea, nausea, and vomiting), while long-term complications are hypercalcemia, lipid profile change, urolithiasis, gallstone, and hair loss [28]. As the trial studies have been done for a short time ((12 weeks) [21], (6 weeks) [22]) and reported the beneficial effects of the ketogenic diet without any adverse complications, our trial will be conducted for short time (8 weeks) as well. The dietitian will also announce each participant of the complications of their diet and remind them to stop their diet if they feel any adverse effects or discovered they are pregnant.

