### Frequency and plans for auditing trial conduct {23}

It is anticipated that every week, the project management group will meet to review trial conduct.

Also, the trial steering group as well as the independent data monitoring and ethics committee will meet to review conduct throughout the trial period, once every 2 weeks. In addition, the trial steering group (Iranian Steering Committee for Clinical Trials) as well as the independent data monitoring committee will observe the day-to-day progress of this trial. The ethics committee of the Kermanshah University of Medical Sciences will control the authenticity of the trial. The faculty of Nutritional Sciences and Food Technology is responsible for the scientific requirements.

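### The harms section sorts adverse events into serious and non-serious by how long they take to appear, and the protocol does not settle whether the committee receiving serious reports is independent

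*Protocol article*

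**What the plan says.** Under Adverse event reporting and harms {22}, the protocol article names two groups of ketogenic-diet effects. The first is "some adverse events (AEs) such as dehydration, hypoglycemia, lethargy, and gestational side effects (diarrhea, nausea, and vomiting) for a short time". The second is "serious adverse effects (SAEs) like hypercalcemia, lipid profile change, urolithiasis, gallstone, and hair loss for long-term intervention". From the 8-week duration it predicts that no SAEs will occur. Participants are to be told of side effects and reminded to stop the diet if they have any AE. The section then states: "SAEs will be reported to the DMEC, indicating expectedness, seriousness, severity, and causality".

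The same effects appear earlier, under Criteria for discontinuing or modifying allocated interventions {11b}, without any grading of seriousness: "Short-term complications are dehydration, hypoglycemia, lethargy, and gestational side effects (diarrhea, nausea, and vomiting", and "long-term complications are hypercalcemia, lipid profile change, urolithiasis, gallstone, and hair loss".

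On the committee, the whole text under the heading for its composition, role and reporting structure {21a} is: "All research team members will collaborate in preparing all the study steps". Under Frequency and plans for auditing trial conduct {23}, by contrast, "the independent data monitoring and ethics committee will meet to review conduct throughout the trial period", every 2 weeks.

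**The concern.** Whether an event is serious depends on what happened to the participant, not on how long the diet had been followed. Section {22} ties the SAE label to long-term exposure and the AE label to short-term exposure. Two consequences follow.

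- The effects that the protocol itself regards as possible within 8 weeks all carry the non-serious label in advance. Staff who read the section as guidance could file a serious episode of dehydration or hypoglycemia as an AE, and the section gives no reporting route for AEs.
- Hair loss and lipid profile change are named as serious by type. Lipids are also a secondary outcome of the trial, so one quantity appears both as an outcome and as an example of an SAE.

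The second issue is who reads the reports. The trial is open, and the composition item mentions only the research team, so the independence claimed in {23} is not secured by the section that should secure it.

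**Working it through.** No arithmetic applies. The check sets the sections side by side.

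**Step 1: match the two lists.**

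| Effect | Label in {11b} | Label in {22} |
|---|---|---|
| Dehydration | short-term | AE |
| Hypoglycemia | short-term | AE |
| Lethargy | short-term | AE |
| Diarrhea, nausea, vomiting | short-term | AE |
| Hypercalcemia | long-term | SAE |
| Lipid profile change | long-term | SAE |
| Urolithiasis | long-term | SAE |
| Gallstone | long-term | SAE |
| Hair loss | long-term | SAE |

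All four short-term entries became AEs and all five long-term entries became SAEs, without exception. Severity or outcome does not explain the split, because hair loss is on the serious side and dehydration and hypoglycemia are on the other. The only attribute that separates the lists is duration.

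**Step 2: see whether the protocol relies on the labels.** It does. The prediction of no SAEs is drawn from the 8-week length alone. That follows only if a serious event needs long exposure.

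**Step 3: trace the reporting route.** SAEs go to the DMEC. For AEs, the section describes what the participant is told to do and gives no route to any committee. Each SAE report must state seriousness, but that happens only after an event has been classed as an SAE. It does not correct an event that was filed as an AE at the start.

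**Step 4: check the lipid item against the outcomes.** The Secondary outcomes section lists "lipid profile (cholesterol, triglycerides, low-density lipoprotein (LDL), high-density lipoprotein (HDL" and the other lipid measures as assessed before and after the intervention. Naming lipid change as an SAE by type therefore overlaps with a planned outcome.

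**Step 5: compare the committee texts.** The sentence under {21a} is identical to the one under the steering-committee item {5d}. It names the research team and nobody else. Section {23} calls the data monitoring committee independent twice, once for its fortnightly meetings and once for observing daily progress. Section {22} does not spell out DMEC. The body whose name fits is the data monitoring and ethics committee of {23}, and I take it to be the committee that {21a} is meant to describe.

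**The case against.** The strongest reply is that {22} gives no definition of an SAE. Both lists are introduced as examples of known diet effects, and a formal definition may well sit in the full protocol that the article condenses. The sentence on reporting to the DMEC has no time limit, requires seriousness to be stated, and provides for SAEs despite the forecast that none will occur. The committee is also said to review conduct every 2 weeks. All of this stands, and it rules out three stronger readings that a reader might infer.

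- *Short-term events cannot be reported, however severe.* No section says so. The DMEC route is stated for SAEs, but nothing bars an acute event from being classed as one, and nothing says the committee sees only SAEs.
- *Any lipid change in any of the 46 women is an SAE.* The section ties lipid change to long-term use of the diet, and this trial lasts 8 weeks. One cannot apply duration to keep acute events out and then ignore it to bring 8-week lipid changes in.
- *The monitoring committee is the research team.* Section {21a} does not say this. It is a general sentence that does not answer its own heading.

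The reply does not remove the fault in the text that is present. The labels follow duration, the forecast depends on that, and the composition item sits badly with the claim of independence. These are points stated wrongly or inconsistently, not details left to a longer document.

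**Conclusion.** Wrong as written, on two counts. First, {22} treats long-term as if it meant serious, for all nine entries it lists, and infers from this that an 8-week trial will have no SAEs. Second, {21a} and {23} do not agree on who forms the data monitoring committee: one names only the research team, the other calls the committee independent.

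The consequence is a risk of misclassifying serious acute events; it is not a stated exclusion of them. Its size cannot be given in events, because the documents report no rates. The weight outcome and its analysis are not affected. The conclusion assumes that staff would take the labels in {22} as guidance, and that the DMEC of {22} is the committee described in {23}. If the full protocol defines SAEs by the seriousness of the individual event, the practical risk is smaller, but the article's text would still contradict that definition.

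**What to change.** In {22}:

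- State that each event is classed as serious or not by the seriousness of that individual event, whatever its timing and whichever diet the participant follows.
- Present the two lists as short-term and long-term effects, as {11b} does, and remove the AE and SAE labels from them. In particular, do not name lipid profile change or hair loss as SAEs by type; lipid change is already handled as a laboratory outcome.
- Delete the inference from the 8-week duration to an absence of SAEs.

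In {21a}, replace the general sentence with a description that agrees with {23}, so that the body receiving SAE reports is the independent committee described there. Use one name for it throughout.

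The cost is wording only, with no change to sample size, visits, measurements or analysis, provided the independent committee in {23} is in place as stated.
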